#### 3.3.2. Micronutrient status

In order to avoid additional invasive blood draws in at-risk equity-deserving patient populations, alternative yet validated measures of individuals’ micronutrient status will be implemented. Both skin carotenoids and urine metabolites can be utilized to define the baseline dietary habits of all participants. Resonance Raman Spectroscopy (RRS) has emerged as an inexpensive and non-invasive tool commonly used to measure skin carotenoid levels including alpha-carotene, beta-carotene, beta-cryptoxanthin, lycopene, lutein, and zeaxanthin (71, 72). Due to the high concentrations of carotenoids in fruits and vegetables, RRS has been used to reliably estimate dietary intake of such foods (71, 72). Its performance has been assessed across multiple geographies and in patients with varied skin tones, and a statistically significant correlation was not identified (71, 72). Similarly, urine metabolites can be assessed using standard laboratory biochemistry commonly available to study centres and can be utilized to estimate the remaining components of diet (73, 74). Consumption habits of fruits, vegetables, low fiber grains, fish protein, nuts, red meat, shellfish, dietary supplements, caffeine, alcohol, and fats and oils can be estimated and corroborated using relative levels of urine metabolites including methyl glutamate, mannitol, cytosine, suberate, omega 3, tryptophan, xylitol, lysine, creatine, vitamin B2, and vitamin E (73, 74). Micronutrient status assessment will be carried out at baseline and at study end to ensure significant micronutrient derangements have not occurred (Figure 3).

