### 2.6. Statistical analysis

#### 2.6.1. Sample size calculation

This is a novel RCT addressing the implications of a WFPBD on neuropathic outcomes in individuals with leprosy. This relationship has not been directly assessed in the current body of literature, however similar research questions have been assessed in individuals with diabetes mellitus. As such, the sample size calculation herein will utilize this literature as a proxy. The efficacy of a WFPBD diet on neuropathy in a diabetes cohort has been reported via the Michigan Neuropathy Screening Instrument (MNSI), including both subjective (questionnaire) and objective (physical assessment) measures. The sample size calculation was based on the MNSI questionnaire measurement as explicit details pertaining to the MNSI physical assessment were not provided. Specifically, both the type of QST utilized (vibration, perception, both, etc.) and the location the test was carried out (lesion, glove, stocking, etc.) were not mentioned. Therefore, the MNSI questionnaire was preferentially chosen as a proxy. Participants receiving the intervention reported a final mean MNSI questionnaire of 5.3 ± 2.5 compared to 7.1 ± 2.8 in the control group at study end (19). Using an opensource sample size calculator with two independent study groups, continuous endpoints, an alpha of 0.5 and 80% power, a final sample size of approximately 60 participants was ascertained (53, 54). This is a conservative estimate as source literature demonstrated a statistically significant effect on outcomes with a relatively low population of 34 individuals (19). Assuming high acceptability and a 14% withdrawal and/or loss to follow-up rate based on previous literature, a final sample size of ~70 individuals, 35 per group, will be needed to adequately power this trial (19, 47, 55, 56).

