#### 2.6.2. Continuous and categorical variables

Descriptive statistics including reported means ± standard deviation for continuous variables [questionnaires including MNSI-physical assessment, Neuropathy Total Symptom Score (NTSS), modified Medical Research Council Scale (mMRCS), Neuropathic Pain Symptom Inventory (NPSI), McGill Pain Questionnaire (MPQ), Pittsburgh Sleep Quality Index (PSQI), and International Physical Activity Questionnaire (IPAQ) summative scores, visual analog scale (VAS), anthropometrics, diabetes duration, hemoglobin A1c, and serum micronutrient levels] and proportions for categorical variables [number of adverse events, dietary adherence, insulin use, leprosy clinical status (according to the WHO and Ridley Jopling classification systems), frequency and prevalence of inflammatory leprosy reactions, corticosteroid use] will be reported by each study group (57). Between- and within-group comparisons will also be made for continuous variables using the Student’s *t*-test with reported *p*-values, and for categorical variables using the chi square or Fisher’s exact tests, reporting *p*-values with odds ratios and 95% confidence intervals. Statistics will also be reported for all time points including baseline, and end of study. Multivariate logistic regression adjusting for covariates [such as age, sex, PROGRESS+ factors (58, 59), level of physical activity, smoking status, alcohol consumption, comorbidities, diabetes status] and potential effect modifiers (such as change in weight over time, medication de-escalation over time) will be carried out to ascertain the impact of a WFPBD on PNP in leprosy patient sub-populations and under various conditions. All statistical analysis will be carried out using GraphPad Prism 8 (GraphPad, United States).

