### 3.3. Secondary outcomes

#### 3.3.1. Anthropometrics, sleep quality, physical activity, and diabetes control

As a dietary lifestyle intervention can have a drastic effect on anthropometrics, height and weight will be measured at both baseline and at the end of the study and will be used to calculate body mass index (BMI) (Figure 3). Likewise, sleep quality has been associated with neuropathy severity, and must be monitored throughout the trial. The Pittsburgh Sleep Quality index is a validated questionnaire, widely used to assess sleep perturbation due to various etiologies. Participants can be assigned a maximum of 21 points indicating severe difficulties in all areas of sleep quality (67). The PSQI will be collected at baseline and at the end of the study. Self-reported physical activity will also be collected at such intervals using the International Physical Activity Questionnaire. The IPAQ includes 27-items designed to gauge the frequency and intensity of physical activity carried out in a 7-day period, encompassing occupational, transportation, housework, and leisure activities. It has been extensively tested and validated throughout 12 countries and has previously been utilized in assessing self-reported physical activity in both diabetes and leprosy cohorts (68–70). To avoid the potentially confounding effects of additional lifestyle levers, such as sleep quality and exercise, these assessments are paramount during downstream analysis. Lastly, in individuals experiencing a biochemical diabetes due to leprosy related corticosteroids, an assessment of diabetes control including duration of illness, therapeutics used, and insulin status will also be carried out to monitor any changes throughout the trial (Figure 3). Standard biochemistry, including serum cholesterol, triglycerides, hemoglobin-A1c, serum glucose, hepatic transaminases, creatinine, and basic micronutrient panel (e.g., serum ferritin, B12) will be taken to measure diabetes parameters and general physiological status. To better ascertain the relationship between the dietary lifestyle intervention and leprosy itself, neuropathy and neuropathic pain outcomes will be stratified by secondary outputs, with specific emphasis on diabetes status, and steroid use.

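### The stated micronutrient analysis, t-test p-values on group means, cannot support the stated aim of showing that no significant derangement occurred

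*Protocol article*

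**What the plan says.** Section 3.3.2 gives the purpose of the assessment: "Micronutrient status assessment will be carried out at baseline and at study end to ensure significant micronutrient derangements have not occurred". It does not define what counts as significant. To spare participants extra blood draws, the section says that "alternative yet validated measures of individuals’ micronutrient status will be implemented", and it describes skin carotenoids and urine metabolites.

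Section 3.3.1 separately plans blood tests, including a "basic micronutrient panel (e.g., serum ferritin, B12) will be taken to measure diabetes parameters and general physiological status".

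Section 2.6.2 lists "anthropometrics, diabetes duration, hemoglobin A1c, and serum micronutrient levels" among the continuous variables, to be summarised as mean ± SD by group. The method is: "Between- and within-group comparisons will also be made for continuous variables using the Student’s *t*-test with reported *p*-values". In that same sentence, categorical variables receive odds ratios and 95% confidence intervals, but no interval is stated for continuous variables. Micronutrient deficiency is not in the list of categorical variables.

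**The concern.** The aim is a statement of absence: no important derangement happened. The stated method tests whether mean levels differ. The two do not fit, for two reasons.

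- A non-significant difference in means does not exclude a relevant fall, least of all in a small trial with no margin and no interval.
- Derangement happens to individuals. If a few participants become deficient and the rest do not change, the mean moves little.

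The diet omits animal products for 24 weeks, and section 1 names cobalamin among the nutrients needed for myelin synthesis. A missed deficiency would therefore bear on neuropathy, the condition under study. Sections 2.2 and 5 present the diet as potentially low-risk, and a bare report of no significant change in micronutrients could be taken as support for that.

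**Working it through.** **Inputs from the article (section 2.6.1).** The sample size rests on a "final mean MNSI questionnaire of 5.3 ± 2.5 compared to 7.1 ± 2.8 in the control group at study end", with "an alpha of 0.5 and 80% power, a final sample size of approximately 60 participants was ascertained", and a "14% withdrawal and/or loss to follow-up rate". No size calculation is given for micronutrients.

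**The plan's own figure.** Using n per arm = 2 × [SD × (z for alpha + z for power) / difference]², with two-sided alpha 0.05, 80% power, difference 7.1 − 5.3 = 1.8 and SD 2.5:

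2 × [2.5 × (1.960 + 0.842) / 1.8]² = 30.3 per arm, rounded up to 31, total 62. This is close to the stated 60.

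The printed alpha of 0.5 gives 9 to 12 per arm, depending on the SD, so it does not reproduce the figure. I use 0.05. Then 60 / (1 − 0.14) = 69.8, or 70 randomised. About 30 evaluable per arm is therefore the right basis.

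**Between-group t-test, 30 per arm.** The noncentrality is d × √(n/2), where d is the mean fall in SD units. There are 58 degrees of freedom and the critical value is 2.002.

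- d = 0.5: 0.5 × √15 = 1.94, and the test is non-significant in 52% of trials. With all 35 per arm it is 46%.
- d = 0.3: 0.3 × √15 = 1.16, non-significant in 79%.
- The 95% CI half-width is 2.002 × √(2/30) = 0.52 SD. An observed difference of zero would still be compatible with a mean fall of about half an SD.

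**Within-group paired t-test, 30 in the diet arm.** The article gives no baseline-to-end correlation, so I assume 0.5 and 0.7. The standardised change is d / √[2(1 − correlation)], and the noncentrality is that value times √30. The critical value is 2.045.

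| Mean fall | Correlation 0.5 | Correlation 0.7 |
|---|---|---|
| 0.5 SD | 25% missed | 7% missed |
| 0.2 SD | 81% missed | 72% missed |

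**Falls confined to a few participants.** This is a simulation of 40,000 trials with unit-SD normal values. The patterns are assumptions; the article gives none. The affected participants are either drawn at random at the stated rate or fixed in number (5 or 3 of 30).

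| Pattern in the diet arm | Between-group, missed | Within-group, missed (correlation 0.7 to 0.5) |
|---|---|---|
| 1 in 6 falls by 1.5 SD | 86% to 87% | 74% to 82% |
| 1 in 10 falls by 2 SD | 90% to 92% | 83% to 89% |

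**What counting can show.** With no new case among m participants who start within range, the exact two-sided 95% upper limit is 1 − 0.025^(1/m). For m = 30 this is 11.6%. If fewer start within range it is higher: 13.7% for m = 25 and 16.8% for m = 20.

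**The case against.** - **No decision rule is stated.** A reader might infer that the trial will treat p > 0.05 as proof of nutritional safety. The article never says so, and its use of significant may mean clinically significant. This stands: the misreading is a risk, not a plan. A clinical meaning would, however, call for an individual cut-off, which a t-test does not supply.
- **It is not the only safety check.** A reader might take the micronutrient assessment as the sole protection against depletion. It is not. Section 3.2.7 assesses adverse events, drop-out and harms at each counseling session, and section 3.3.1 adds weight and biochemistry. This stands. The micronutrient measures are still the direct check of nutrient status.
- **Aim and analysis sit with different markers.** The aim closes a section on skin and urine markers. The analysis section names serum levels, and the serum panel has another stated purpose. This stands as a discrepancy to reconcile. The t-test covers the skin and urine markers only through the general wording on continuous variables.
- **Within-group tests are more sensitive.** This is true for a uniform 0.5-SD fall, where they detect 75% to 93%. It does not hold for small mean falls or falls in a few participants.
- **Cut-offs and listings may be in documents not shown.** They may, and values are recorded per participant, so it is not established that individual deficiencies would go unseen. Their absence from the article is not the point here. The point is that the method the article does state does not serve the aim it states.
- **Counting does not create power.** Correct: at 30 per arm, Fisher's exact test has 9% power for 5% versus 15% and 24% for 5% versus 20%. The gain is an honest estimate with an upper limit, not a powered test.

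**Conclusion.** The point holds as a mismatch between aim and method. T-test p-values on means, at about 30 evaluable per arm, cannot support a conclusion that no derangement occurred. The between-group test misses a 0.5-SD mean fall about half the time. When only a few participants are affected, both tests usually miss it.

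The 52% figure rests on alpha 0.05 and 30 per arm. The within-group figures also rest on the assumed correlations, and the few-participant figures on assumed patterns and normal values. Serum markers may be skewed, which the simulation does not model.

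The documents do not support the stronger claims that non-significance will be taken as proof or that deficiencies will go unrecorded. The outcome is secondary and the primary efficacy result is unaffected. This is a worthwhile, inexpensive improvement.

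**What to change.** In sections 2.6.2 and 3.3.2:

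1. For each serum marker with a laboratory reference range (for example ferritin and B12), report by arm the number and proportion below the lower limit at baseline and at study end. Also report the number newly below it among those within range at baseline. Give exact 95% CIs, and the between-arm risk difference with its 95% CI. Showing both visits keeps participants who were already low at baseline in view.
2. Report mean change, including for the skin and urine markers, as a baseline-adjusted between-arm difference with a 95% CI. State that p > 0.05 is not evidence of no derangement.
3. Reword the aim in section 3.3.2 from ensuring absence to estimating the frequency of new deficiency, with its upper 95% limit.
4. Make sections 2.6.2, 3.3.1 and 3.3.2 agree on which markers, serum or skin and urine, serve this aim, and state that the serum panel is taken at both visits. Section 3.1 implies this timing, but section 3.3.1 does not state it.

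The cost is wording and a simple table from values already planned for collection, with no new participants or samples. The safety statement becomes more modest: even no new case among 30 within-range participants leaves rates up to 11.6% open, and more if fewer start within range.

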### 3.4. Potential stratifiers/confounders

Beyond primary and secondary endpoints, potentially confounding variables will be collected and utilized for downstream data analysis including: (1) demographic data: age, sex, socioeconomic status [relative within country and absolute according to World Bank definitions (75)], occupation (considering level of manual work, repetitive tasks, and prolonged standing/walking/climbing), household membership (living alone vs. with family members), and education level; and (2) lifestyle-related information: level of physical activity (via the international physical activity questionnaire), tobacco and cannabis smoking and alcohol consumption habits (amount consumed/day), and environment (urban vs. rural; meters a.s.l.). Effect modifiers including weight loss over time and de-escalation of medication over time will also be considered. Considerations of intervention cost, feasibility, cultural acceptability, and adherence will also be collected and summarized in a thematic analysis (Figure 3).

## 4. Ethics, dissemination, and access

In advance of study initiation and following Research Ethics Board (REB) approval at all participating centers, this trial will be registered with ClinicalTrials.gov clinical trial database (76) according to the Interventional Trial Protocol Registration Template.^1^ Current literature suggests high acceptability, and a limited risk profile associated with a WFPBD (19, 21, 22, 47, 55, 56). As a result, a safety board will not be established, however, data on relevant safety, tolerability, and harms will still be collected for downstream analysis. Iterative updates to the trial protocol will be made available to the REB and trial updates will be populated within the ClinicalTrials.gov website as soon as they become available. Data, protocol updates, and study progress will be made available to relevant stakeholders including the site principal investigators, study personnel, and participants, and will be disseminated in the form of peer-reviewed journal publications, submitted conference abstracts/posters, presentations, and lay-language infographics.

## 5. Expected impact

This trial aims to investigate the potential neuro-protective impact of a WFPBD on sensory and motor neuropathy in leprosy, thereby strengthening the literature underpinning dietary lifestyle interventions for chronic diseases. Through comprehensive validated questionnaires and QST, a robust profile of neuropathy progression and the relative impact of a WFPBD will be ascertained. Given this assessment, this trial has the potential to inform on the development of novel guidelines to better manage the sequelae of leprosy, an infectious disease of significant global relevance. Patients experiencing a leprosy infection continue to suffer from debilitating therapeutic side effects and social ostracization, contributing to ever rising disability-adjusted life years (DALYs) lost (6, 77–79). Therefore, a WFPBD in the management of leprosy-related neuropathy may mitigate the significant impact of the disease at both the patient and economic level. A WFPBD has the potential to serve as a low-risk, low-cost, low-tech intervention for chronic neuropathic pain, improving function and reducing the overall morbidity of leprosy. More broadly, this trial will also contribute to the growing literature regarding the importance of dietary lifestyle interventions in disease management and may lead to the continued investigation of this relationship in other diseases of relevance.

## Data availability statement

The original contributions presented in the study are included in the article/supplementary material, further inquiries can be directed to the corresponding author.

